## Abstract

**Background:**

Glioblastoma (GBM) is a highly virulent tumor of the central nervous system, with a median survival < 15 months. Clearly, an improvement in treatment outcomes is needed. However, the emergence of these malignancies within the delicate brain parenchyma and their infiltrative growth pattern severely limit the use of aggressive local therapies. The particle therapy represents a new promising therapeutic approach to circumvent these prohibitive conditions with improved treatment efficacy.

**Methods and design:**

Patients with newly diagnosed malignant gliomas will have their tumor tissue samples submitted for the analysis of the status of O-6-methylguanine-DNA methyltransferase (*MGMT*) promoter methylation. In Phase I, the patients will undergo an induction carbon ion radiotherapy (CIRT) boost followed by 60 GyE of proton irradiation with concurrent temozolomide (TMZ) at 75 mg/m^2^. To determine the maximal dose of safe induction boost, the tolerance, and acute toxicity rates in a dose-escalation manner from 9 to 18 GyE in three fractions will be used. In Phase III, GBM-only patients will be randomized to receive either 60 GyE (2 GyE per fraction) of proton irradiation with concurrent TMZ (control arm) or a CIRT boost (dose determined in Phase I of this trial) followed by 60 GyE of proton irradiation with concurrent TMZ. The primary endpoints are overall survival (OS) and toxicity rates (acute and long-term). Secondary endpoints are progression-free survival (PFS), and tumor response (based upon assessment with C-methionine/fluoro-ethyl-tyrosine positron emission tomography [MET/FET PET] or magnetic resonance imaging [MRI] and detection of serologic immune markers). We hypothesize that the induction CIRT boost will result in a greater initial tumor-killing ability and prime the tumor microenvironment for enhanced immunologic tumor clearance, resulting in an expected 33% improvement in OS rates.

**Discussion:**

The prognosis of GBM remains grim. The mechanism underpinning the poor prognosis of this malignancy is its chronic state of tumor hypoxia, which promotes both immunosuppression/immunologic evasion and radio-resistance. The unique physical and biological properties of CIRT are expected to overcome these microenvironmental limitations to confer an improved tumor-killing ability and anti-tumor immune response, which could result in an improvement in OS with minimal toxicity.

*Trial registration number* This trial has been registered with the China Clinical Trials Registry, and was allocated the number ChiCTR-OID-17013702.

## Background

Glioblastoma (GBM) is the most biologically aggressive and the most commonly diagnosed primary tumor of the brain. It is characterized by a rapid progression and diffuse infiltration of the brain parenchyma. While a modest improvement in overall survival (OS) was achieved with the addition of temozolomide (TMZ), which has now become the standard of care, the expected median survival remains dismal at around 15 months [1]. Attempts at intensifying the TMZ dosing has proved to be ineffective [2]. Numerous lines of investigation on alternative treatments, both historical and ongoing, have included boron capture therapy, altered radiotherapy fractionation, polychemotherapy regimens, vaccination, and targeted biological agents, but all have failed to become the standard of care. Clearly, alternative approaches are needed to improve the outcomes of these patients.

### GBM-tumor hypoxia and immunology

A hallmark characteristic of GBM is the presence of tumor cell hypoxia. From a cancer biology and tumor evolution perspective, hypoxia is a physiologic stressor that promotes the selection of a more aggressive phenotype exhibited by aberrant cell populations. Severe hypoxia is known to induce an increased invasiveness, dysregulated angiogenesis, increased mutagenicity, altered metabolism, and increased proliferation of GBM tumor cells [3–5]. From an anti-tumor perspective, hypoxia significantly limits the effectiveness of TMZ chemotherapy, and that of photon-based radiotherapy, which relies on oxygen-derived free-radical species to confer an indirect DNA damage towards killing tumor cells. This enhances the expression of stem cell markers, as stem-like properties impart great cellular resistance to all types of cytotoxic therapy [6, 7]. Lastly, the condition of chronic hypoxia can lead to an inhibition of both innate and adaptive antitumor immune responses [8–10].

### Physical and biological characteristics of carbon ion radiotherapy in cancer treatment

Charged-particle therapy, such as proton radiotherapy (PRT), helium therapy, and carbon ion radiotherapy (CIRT), possesses distinct physical characteristics that make it superior to photon therapy. These characteristics include a sharp lateral penumbra; minimal energy deposition within the beam’s entry path prior to the Bragg peak, which is defined by its steep dose deposition; and a sharp dose-deposition fall-off after the Bragg peak. Thus, charged-particle beams exhibit both a precise and a finite range with respect to their dose delivery capability. The depth of the Bragg peak can be altered by altering the particle beam’s energy. These properties enable the sparing of surrounding normal tissues, which is crucial when irradiating the brain and its critical structures. Several reports have shown improved dose distributions using particle therapy for primary or recurrent glioma, with a suggested improved efficacy and acceptable toxicity profiles [11–13].

In addition to its superior dosimetric properties, a heavy ion such as the carbon ion is a high linear energy transfer (LET) modality. Furthermore, the relative biological effectiveness (RBE) of CIRT is substantially higher than that of photon- and proton-based irradiation. The value of RBE is suggested to be 3–5 for carbon ion. The actual calculated value is dependent on both the tissue type and the biological endpoint of RBE assessment. High-LET irradiation inflicts more damage via direct DNA double-strand breaks, which are more difficult to repair [14]. Improved efficacy could be expected after the delivery of high-LET radiation, such as CIRT, especially in the treatment of photon-resistant cancer cells that have been selected for their ability to more efficiently repair single-strand DNA breaks. Furthermore, several in vitro studies have shown greater tumor-killing efficiency in GBM and, more importantly, in glioma stem cell lines by CIRT when compared to photon radiotherapy or PRT [15–18]. Per convention with CIRT (and other particle-based modalities), the differences in RBE and LET between CIRT and photon radiotherapy is taken into account, and the CIRT doses are reported in terms of gray equivalents (GyE), which refer to the biological effective doses (BEDs) of photons.

The efficacy of CIRT is also much less hindered by hypoxic conditions as compared with photon or proton radiotherapy, which predominate in GBM tumors [19–21]. This, in turn, leads to a greater tumor cell killing efficiency, especially in the early course of treatment, when the greatest number of residual tumor cells are present within the unresected tissue, and along with postoperative tissue reaction, the greatest extent of tumor hypoxia is encountered during the radiotherapy course. Not only does the more densely-ionizing CIRT lead to a greater proportion of tumor cells being killed, the mechanism of cell death is significantly different when compared with conventional, low-LET irradiation, which includes greater ability of inducing the ceramide pathway and increasing complex double-stranded DNA damage which leads to greater autophagy, apoptosis, and mitotic cell death [22–25]. Not surprisingly, this enhanced mode of cellular destruction releases more tumor-specific antigens, is more immunogenic, and fosters a stronger local/direct and abscopal antitumor immune response [26–28].

### Clinical experience of CIRT—safety and efficacy

Results from retrospective and prospective studies have shown improved outcomes after CIRT for several malignancies, including chordoma/chondrosarcoma of the skull base [29–31], melanoma [32], and adenoid cystic carcinoma of the head and neck region. These results also demonstrated the safety of CIRT in protecting the critical organ-at-risks (OARs), such as the optical nerve/chiasm, brain, brainstem, and spinal cord. At the Heidelberg Ion-Beam Therapy Center (HIT) and the National Institute of Radiological Sciences (NIRS) in Japan, CIRT is currently the routine treatment for patients with these mentioned conditions.

### Induction CIRT boost rationale

The novel approach of administering the CIRT boost prior to the initiation of standard, low-LET-based chemoradiotherapy has the following multiple theoretical advantages:Overcoming hypoxia. In the postoperative setting, the number of residual tumor cells and level of hypoxia are at their greatest extent, whereas CIRT can overcome such hypoxic conditions [29];Targeting glioma stem cells earlier in the treatment course. This enables the radiation-naïve stem cells to receive large-fraction doses of the more-effective high-LET irradiation before they can develop radio-resistance to smaller factions of low-LET radiotherapy;Altering the cell death mechanisms/immunogenicity. CIRT can shift the pro-/anti-tumor immunologic balance towards anti-tumor immunity at the beginning of radiotherapy, as opposed to being given after the immunosuppressive TMZ and conventional fractions of low-LET radiotherapy have been delivered;Treatment compliance. Patients are more likely to receive the entire prescribed CIRT dose if it is given first. Fatigue and toxicity of the 30-fraction PRT course could potentially dissuade continued treatment;CIRT responses. Assessing the CIRT-specific responses (imaging and immunologic assays) is less confounded by standard PRT. The biological effect of CIRT differs from that of low-LET PRT and the administration of CIRT boost prior to standard chemoradiotherapy would reduce the interference of other factors to detecting CIRT-specific responses.

## Methods and design

### Study design

The purpose of this trial is to first determine, in a Phase I dose escalation study, the maximal safe induction CIRT boost to the residual tumor in malignant glioma patients [GBM or anaplastic astrocytoma (AA)] that can be given to patients in addition to adjuvant radiotherapy at the standard dose (i.e., 60 GyE in 30 fractions). The rationale for this approach is to provide a different form of radiotherapy; one with a higher LET, having a different mode of tumor-killing, and possessing a greater overall tumor-killing ability due to its weaker dependence on oxygenation for efficacy, to the site of disease immediately after surgery when the number of tumor cells and extent of hypoxia are at their greatest. We anticipate that these factors will result in a shift from the usual pro-tumor immunosuppression, fostered by tumor microenvironment, into one that promotes a greater inflammatory and anti-tumor immunity environment.

In the second stage of this trial, the Phase III, the following hypothesis will be tested: When induction CIRT boost with the maximal safe dose (determined in Phase I) is given prior to standard PRT, whether this strategy will result in a prolonged OS of GBM patients without provoking additional toxicity as compared with standard PRT.

A secondary aim of this study is to determine if there are immunologic response profile differences between those receiving CIRT boost and those who do not, such that additional immunotherapeutic agents can be administered in future trials to synergize and augment the effects of the CIRT boost.

### Ethics, informed consent, and safety

All clinical trials of the SPHIC, including the present trial, are required to adhere to the policies set forth by the Institutional Academic Committee and the Institutional Review Board (IRB). IRB approval of the current trial was obtained. The following sections were adapted and summarized from the institutional policies on human studies to which the present trial will adhere.

The IRB of the Shanghai Proton and Heavy Ion Center (SPHIC) independently monitor the recruitment, the reporting of adverse events, and the data quality for all clinical trials. Data and interim results for this trial will be reviewed semi-annually according to the trial protocol. The IRB will provide the principal investigator with requirements and recommendations on the modification of the trial, which may or may not include termination of the trial.

The study will be conducted according to the Chinese guidelines for good clinical practice (GCP) and the principles of the Declaration of Helsinki (2008 version, adopted at the 59th World Medical Association General Assembly, Seoul, Korea, October 2008).

### Trial design

#### Phase I

In this initial portion of the study, the maximal tolerable dose (MTD) of the induction CIRT boost will be determined. Anaplastic astrocytoma (AA) will be allowed to be included in the Phase I study, as it will expedite the accrual time and considering that this tumor is treated identically as to GBM at our institution. The starting boost dose will be 9 GyE in 3 fractions for the first three patients enrolled. In the absence of any severe (defined as ≥ grade 3) acute toxicities [dose-limiting toxicity (DLT)] assessed using the Common Terminology Criteria for Adverse Events (CTCAE) v. 4.03, the next 3 patients will receive 12 GyE in 3 fractions (i.e., 4 GyE × 3 fractions). Further dose escalation will be continued to 15 GyE then the maximal 18 GyE in 3 fractions (i.e., 5 GyE then 6 GyE × 3 fractions). The MTD will then be used in the experimental arm in Phase III of this trial. If there is one case of ≥ grade 3 acute toxicity within a dosing group, 3 more patients will be added to this group. If 2 or more cases of ≥ grade 3 acute toxicities are observed, the boost dose used in the preceding lower-dose group will be chosen. If 9 GyE proves to be too toxic, a CIRT boost of 6 GyE in 2 fractions will be incorporated into the experimental arm. All Phase I patients, after receiving induction boost irradiation, will go on to receive 60 GyE in 30 fractions of PRT with concurrent daily TMZ at 75 mg/m^2^. Table 1 summarizes the Phase I design.

**Table 1 Tab1:** Phase I design of dose escalation of induction carbon ion boost for treating GBM and AA

Remarks	Boost set	Induction carbon ion Boost			Cumulative BED^*^ (GyE)		EQD2^*^ (GyE)	
		Dose/Fx (GyE)	No. of Fx	Total dose (GyE)	Tumor (α/β = 10)	Brain (α/β = 3)	Tumor (α/β = 10)	Brain (α/β = 3)
Phase I starting dose	1	3	2	6	79.8	112.0	66.5	67.2
	2	3	3	9	83.7	118.0	69.8	70.8
	3	4	3	12	88.8	128.0	74.0	76.8
	4	5	3	15	94.5	140.0	78.8	84.0
	5	6	3	18	100.8	154.0	84.0	92.4
PRT regimen	N/A	0	0	0	72.0	100.0	60.0	60.0

*GBM* glioblastoma, *AA* anaplastic astrocytoma, *BED* biological effective dose, *EQD2* equivalent dose for a 2 GyE/fraction treatment, *α/β* alpha/beta ratio, *Fx* fraction, *GyE* gray-equivalents

* The dose of proton radiotherapy (60 GyE in 30 fractions) is included in the calculation of cumulative BED and EQD2

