#### Phase III

##### Experimental arm

A total of 122 patients will be enrolled into this arm and undergo an induction CIRT boost to the residual gross tumor volume. The dose of the induction boost will be determined in Phase I of the trial. One week after the first fraction of the induction boost, a standard PRT (60 GyE in 30 fractions) with concurrent daily oral administration of TMZ at 75 mg/m^2^ will commence.

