### Study objectives

#### Phase I

The primary objective is to determine the maximal safe induction CIRT boost dose.

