### Treatment assignment

The flow chart of this Phase I/III trial is illustrated in Fig. 2. Patients enrolled into Phase I of this trial will be assigned to groups of 3, and each group will receive a progressively increasing dose of induction CIRT boost until the safe dose is determined or the maximal dose of 18 GyE in 3 fractions is reached without ≥ grade 3 toxicities. Patients who later opt out of the study will be replaced by newly enrolled ones. Patients enrolling into the Phase III of this trial will be randomly assigned to either the experimental or control arm (1:1 randomization), as described above. Patients withdrawn from this phase will retain their randomization number, and new patients will be issued with a new randomization number.

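### If 9 GyE fails in Phase I, 6 GyE in 2 fractions goes straight into the Phase III arm without a Phase I cohort at that level

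*Protocol article*

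**What the plan says.** The Phase I section of the protocol article fixes the entry level: "The starting boost dose will be 9 GyE in 3 fractions for the first three patients enrolled". The levels above it are 12, 15 and 18 GyE, all in 3 fractions. One grade 3 or higher acute toxicity in a dose group adds 3 patients to that group. Two or more send the choice back to the level below. The abstract describes Phase I as proceeding "in a dose-escalation manner from 9 to 18 GyE in three fractions will be used", and under Treatment assignment "each group will receive a progressively increasing dose of induction CIRT boost until the safe dose is determined". Neither describes a step down.

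For failure of the entry level itself, the Phase I section says: "If 9 GyE proves to be too toxic, a CIRT boost of 6 GyE in 2 fractions will be incorporated into the experimental arm".

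Three other places tie the Phase III dose to a Phase I result:
- Study design states the Phase III hypothesis for the case where "induction CIRT boost with the maximal safe dose (determined in Phase I) is given prior to standard PRT".
- Study objectives, Phase I: "The primary objective is to determine the maximal safe induction CIRT boost dose".
- Phase III, Experimental arm: "The dose of the induction boost will be determined in Phase I of the trial". This section plans 122 patients for the arm.

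**The concern.** Every other level that can reach Phase III has first been given to a Phase I cohort and has passed the toxicity rule. The 6 GyE fallback is the exception. If 9 GyE fails, Phase I ends with no level having passed, yet Phase III opens. The safe dose would then be inferred from the failure of a higher one and not observed.

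This would happen at the point where caution matters most. The branch is entered only after an observed rate of severe acute toxicity of one third or more at the lowest level studied. The next level down would then be given in a randomised arm of 122 patients, in a trial that has toxicity among its primary endpoints and aims to show no added toxicity. What is at stake is patient safety and the link between the two phases. The log-rank comparison, its type I error and the number of events are not at stake.

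**Working it through.** **1. Where 6 GyE in 2 fractions appears**

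| Place in the protocol article | What it gives for 6 GyE in 2 fractions |
|---|---|
| Abstract, Methods and design | Not in the stated range (9 to 18 GyE, three fractions) |
| Phase I, text | Fallback placed in the experimental arm; no cohort size and no toxicity check |
| Phase I, Table 1 | Listed as boost set 1 with BED and EQD2; no cohort or rule |
| Treatment assignment | Increasing doses only |
| Radiotherapy planning, Table 3 | Boost given as 3 fractions only |

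In Table 1 as extracted, the remark marking the starting dose sits on the 6 GyE row. The text starts at 9 GyE, so this may be a row shift from the extraction. Even read literally, it supplies no cohort or rule.

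**2. Reproducing Table 1**

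With 60 GyE of PRT in 2 GyE fractions and a boost of n fractions of d GyE:

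BED = 60 × (1 + 2/(α/β)) + n × d × (1 + d/(α/β)).

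For brain, α/β = 3:
- PRT alone: 60 × (1 + 2/3) = 100.0
- 6 GyE boost: 100.0 + 6 × (1 + 3/3) = 112.0
- 9 GyE boost: 100.0 + 9 × (1 + 3/3) = 118.0

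All three match Table 1, as do the other BED and EQD2 entries. The 9 GyE boost adds 18 units and the 6 GyE boost adds 12, so 12/18 = 67% of the added brain BED remains after the step down.

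**3. How often the branch is reached**

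The article gives no dose-limiting toxicity rate, so the true rate p is an assumption. A level fails if 2 or more of the first 3 patients have an event, or if 1 of 3 does and at least 1 of the next 3 does:

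P(fail) = [3p²(1 − p) + p³] + 3p(1 − p)² × [1 − (1 − p)³].

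For p = 0.10: 0.028 + 0.243 × 0.271 = 0.0939. For p = 0.20: 0.104 + 0.384 × 0.488 = 0.2914.

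| Assumed true rate | P(level fails) | P(level passes) |
|---|---|---|
| 5% | 2.7% | 97.3% |
| 10% | 9.4% | 90.6% |
| 15% | 18.6% | 81.4% |
| 20% | 29.1% | 70.9% |
| 30% | 50.6% | 49.4% |

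Applied to 9 GyE, the middle column is the chance of entering the branch. Applied to 6 GyE, it is the chance that the same rule would have rejected the fallback, had it been used there.

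**4. What is known once the branch is entered**

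The smallest observed rate that triggers it is 2/6 = 33%. The exact 95% interval for the rate at 9 GyE is 4% to 78% after 2 of 6 events, and 9% to 99% after 2 of 3. No patient has been treated under the 6 GyE schedule.

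**The case against.** The strongest reply is that the fallback is a de-escalation. It is the 9 GyE schedule with one fraction removed, at the same 3 GyE per fraction, so every patient treated at 9 GyE would have received those two fractions and then a third. Lower toxicity is a reasonable expectation, and the dose is chosen by a prespecified rule that uses Phase I results. This stands and keeps the point modest. It does not show that 6 GyE is acceptable: a dose below one that failed may also be too toxic.

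The brain BED figure is also open to challenge, because the article links no BED value to the rate of acute grade 3 or higher events. That is right. The figure shows only that the step down is partial and does not quantify the risk at 6 GyE. The branch probabilities likewise depend on assumed rates, and at 5% to 10% the branch is uncommon (2.7% to 9.4%).

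Safeguards exist: weekly toxicity evaluation, semi-annual IRB review, the possibility of stopping at the interim analysis if benefit/risk worsens, and a between-arm comparison of adverse events. They limit exposure, but all act after Phase III patients have started treatment.

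Finally, an article condenses a fuller protocol, and Table 1 does number 6 GyE among the boost sets. But the article does not leave this branch out. It states the rule and names the experimental arm as the destination.

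**Conclusion.** The concern holds. As written, failure of 9 GyE sends an untested schedule into the Phase III experimental arm, and on that branch the statements that Phase I determines the Phase III dose are not true. The chance of reaching the branch runs from 2.7% to 50.6% for assumed true rates of 5% to 30% at 9 GyE. If 6 GyE itself had a true rate of 10%, 20% or 30%, the cohort rule would have rejected it with probability 9.4%, 29.1% or 50.6%, but the rule is not applied there. These figures rest on the assumed rates and on reading the expansion rule as failure at 2 or more events among up to 6 patients.

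This is a conditional safety gap that should be fixed. It does not affect the validity of the Phase III analysis.

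**What to change.** Amend the Phase I section. If 9 GyE is too toxic, treat a Phase I cohort of 3 patients at 6 GyE in 2 fractions, expanded to 6 under the existing rule, and carry that level into Phase III only if it passes. State that, if it does not pass, Phase III does not open without a protocol amendment. Add the 2-fraction schedule to Table 3, and confirm that the starting-dose remark in Table 1 belongs to boost set 2 (9 GyE).

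The cost now is one or two sentences and two table checks. Only if the branch occurs does it cost 3 to 6 more Phase I patients and a short delay. It also brings a chance that a tolerable dose is rejected and Phase III is held for an amendment (9.4% at a true rate of 10%). The check is a modest one: a cohort this small would still pass a level with a true 30% rate 49.4% of the time. It does put 6 GyE under the same standard as every other level.
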